### Intervention Trial

#### Overview

The intervention trial compares the effectiveness of the iCanFit 2.0 intervention program with a comparator program among overweight older adults in a primary care setting. To achieve this goal, we will conduct a cluster RCT in 12 family medicine clinics (six pairs) in Central Texas, USA. In each pair of comparable clinics, one will be randomized to the intervention group and one to the control group (see Figure 2).

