#### Study Sites and Sources of Patients

We will conduct the proposed trial in 12 family medicine clinics that belong to a large university-affiliated, integrated health care system in Central Texas. These clinics were selected because of their similarity in patient demographics, clinic operation, and service coverage. The 12 clinics will be grouped into six pairs. Clinics in each pair have been selected to have similar characteristics of size (ie, number of patient visits per year) and number of overweight older adults as well as situated miles apart to reduce possible contamination of the intervention. We will use a randomization table to assign the two clinics in each pair into the intervention group or the control group.

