#### Power and Sample Size Calculations

The primary outcome of the study is the total minutes of MVPA per week. MVPA is measured as “very active” and “fairly active” on Fitbit. The secondary outcome of the study is the patient’s self-report quality of life, measured by the 12-Item Short Form Survey [39]. We hypothesize the effect size of the iCanFit 2.0 to be 0.25, based on a prior Fitbit intervention trial [43]. Following the procedure developed by Cohen, the calculation of sample size is carried out in three steps by assuming a .05 significance level to achieve the power of 0.8 [44]. First, we assume that two independent samples can be obtained for the same size *n*_1_ each. Then the total sample size is *n*=2 x *n*_1_. In this ideal scenario, the total sample size *n*=398 is required to detect the effect size *d*=0.25 between the two population means. Second, because the randomization occurs at the clinic level, we need to consider the clustering effect. Previous similar research suggests a small clustering effect due to multiple patients per physician, but virtually no clustering effect between patients with different physicians in the same clinic [45]. We assume that if the intraclass correlation coefficient (ICC) per patient is equal to .05, and that ICC per physician is equal to 0, then equation 1 holds:

ICC=(1 + ICC_patient) x (1 + ICC_physican) – 1 = .05 (1)

Thus, the design effect is as follows in equation 2:

D=1 + (m - 1) x ICC (2)

where m is the average number of patients per physician in our effective sample. If we restrict m to be no more than 6, then D=1 + 5 x .05 = 1.25. We would need a sample size of 498 (ie, 398 x 1.25) after factoring in cluster effects. Third, based on our prior study of RCT primary care settings [36], we assume the attrition rate to be 0.2 after 12 months, thus the required sample size at baseline is 622 in total (ie, 498/[1-0.2]), or 52 patients per clinic on average. We will recruit no fewer than 30 and no more than 70 patients from each participating clinic.

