#### Data Analysis Plan

Our analysis has been planned to correspond to the study’s main aim. We will begin with exploratory data analyses. Demographic and baseline characteristics for the participants will be summarized using descriptive statistics overall and by intervention and control groups to assess baseline comparability. Prior to analyses, we will check continuous outcome distributions and apply normalizing transformation where needed.

Our main goal is to test the hypothesis that patients in the intervention group will have more MVPA per week than the control group. To test this hypothesis, we will compare major outcomes between the intervention and control groups. We will implement multi-level regression models (eg, hierarchical linear models and mixed-effect models). Multi-level regression models are needed to account for an ICC that results from clinic-level observations [45]. Patients’ observations over time are nested within PCPs, and PCPs are nested within clinics.

Equation 3 presents an example of a multi-level regression model for a continuous outcome Y_ijt_, on clinic *i*, PCP *j*, and time point *t*. Our analyses will also include background characteristics that are not included in equation 3 for the sake of brevity. Two predictors, time (TIME) and intervention group (INTV), are classified as 1=iCanFit and 0=control. The multi-level regression model is given as follows:

Y
_ijt_ = α
_0_ + INTV
_i_ × α
_1_ + TIME
_ijt_ × α
_2_ + INTV
_i_ X TIME
_ijt_ × α
_3_ + ζ
_ij_ + ε
_ijt_ (3)

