where α_0_, α_1_, α_2_, and α_3_ are the fixed effects, ζ_ij_ is a random effect (ie, random intercept) for each PCP in each clinic, and ε_ijt_ is the residual error for repeated observations over time. The random effect is assumed to be normally distributed with mean zero. The residual error is assumed to be multivariate normally distributed across repeated observations, with mean zero and a covariance matrix that models the autocorrelation among repeated observations [46]. We will examine model fit statistics to choose an appropriate covariance structure. Hypothesis testing will be carried out to test for intervention effects on the outcome of interest over time. Referring to equation 3, this is equivalent to testing the hypothesis H_0_: α_3_ = 0. If higher outcome values are desirable, then a positive significant α_3_ parameter indicates a positive intervention effect (ie, we reject H_0_: α_3_ = 0). We will use the SAS version 9.0 (SAS Institute Inc) PROC MIXED procedure and PROC GLIMMIX procedure to fit multi-level models to continuous and binary data, respectively.

We will also apply structural equation modeling (SEM) to examine the extent to which the intervention takes effect at individual, interpersonal, health care, and community levels as shown in Figure 1. Models will be constructed to measure direct and indirect effects. We will also analyze whether increased MVPA is a mediator for improved clinical outcomes. Latent variables are similar to random effects, accounting for nested observations. We will use Mplus version 3.1 (Muthén & Muthén) to fit SEM for continuous and binary data [47,48].

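### The model that carries the primary test has only a PCP random intercept, so the group-by-time test has no error term for clinic or PCP variation in change

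*Protocol article*

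**What the plan says.** The Overview of the Intervention Trial describes 12 clinics in six pairs: "In each pair of comparable clinics, one will be randomized to the intervention group and one to the control group". Study Sites and Sources of Patients repeats this: "We will use a randomization table to assign the two clinics in each pair into the intervention group or the control group".

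The Data Analysis Plan gives the reason for its model: "Multi-level regression models are needed to account for an ICC that results from clinic-level observations". It then describes the hierarchy, in which patients' "observations over time are nested within PCPs, and PCPs are nested within clinics".

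Equation 3 contains fixed effects for group, time and group-by-time, a term ζ_ij and a residual ε_ijt. The text explains that ζ_ij "is a random effect (ie, random intercept) for each PCP in each clinic" and that the residual covers repeated observations over time. No clinic, clinic-by-time, PCP-by-time or pair term appears, and Y_ijt has no index for the patient. The intervention hypothesis is H0: α3 = 0, the group-by-time coefficient. The equation is introduced as an example, and the only additions announced are covariates describing the participants.

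Power and Sample Size Calculations takes the ICC as .05 with at most 6 patients per physician. Citing earlier research, it assumes practically no correlation between patients of different physicians at the same clinic.

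**The concern.** The stated purpose of the model and the model itself do not agree. The text asks for clinic-level correlation to be handled, but the equation has nothing at clinic level.

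The tested parameter makes this worse. α3 compares change over time between the arms. An intercept shared by all of a PCP's observations is the same at baseline and follow-up, so it drops out of each patient's change. The one cluster term in the model therefore gives α3 no protection. If clinics differ in how much their patients change, for reasons unrelated to the intervention, that variation enters the estimated effect but not its standard error. With only 12 randomised units, the trial could then report as an intervention effect what is only a difference between clinics.

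**Working it through.** **The plan's own figures.** The inputs are "by assuming a .05 significance level to achieve the power of 0.8", "We hypothesize the effect size of the iCanFit 2.0 to be 0.25" and, for equal arms, "we assume that two independent samples can be obtained for the same size" in each. For a total of 2 × n1:
- One-sided: n1 = 2(1.645 + 0.842)²/0.25² ≈ 198, total 396; about 397 with the t distribution, 398 as an even total. This matches the plan.
- Two-sided: total 504, which does not match.
- 398 × 1.25 = 497.5, stated as 498; 498/0.8 = 622.5, stated as 622; 622/12 ≈ 52 per clinic.

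The chain reproduces with a one-sided .05, although the text does not state the side. That is a separate matter. Two-sided results are given below, with one-sided ones alongside.

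**Why the intercept cancels.** Write patient k's outcome as group and time effects + ζ_ij + ε. The change from baseline to follow-up contains ζ_ij − ζ_ij = 0, exactly so in a balanced layout. The standard error of α3 then treats patients' changes as independent.

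**Size of the effect.** The number analysed per clinic is 498/12 = 41.5. Let ρ be the clinic ICC of change, which the article does not give, so a range is assumed. The true variance of the contrast exceeds the modelled one by about D = 1 + 40.5ρ, and the actual two-sided error is 2(1 − Φ(1.96/√D)):

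| ρ | D | two-sided | one-sided |
|---|---|---|---|
| 0 | 1.000 | 5.0% | 5.0% |
| .005 | 1.203 | 7.4% | 6.7% |
| .01 | 1.405 | 9.8% | 8.3% |
| .02 | 1.810 | 14.5% | 11.1% |
| .05 | 3.025 | 26.0% | 17.2% |

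With no clinic effect, but with the plan's PCP ICC of .05 and 6 patients per PCP applied to change, D = 1 + 5 × .05 = 1.25 and the error is 8.0%. Applying that ICC to change is an assumption; the article does not describe it as an ICC of change.

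**Simulation checks under the null** (12 clinics, 7 PCPs each, 6 patients per PCP):
- Patient change scores, 20,000 runs: 4.9%, 7.2%, 10.0%, 14.7% and 26.0% for the five rows above, and 7.7% for the PCP-only case. With ρ = .01 and a PCP ICC of change of .05 together: 12.5%.
- The same data analysed by clinic mean change: 4.8% to 5.1% throughout, unpaired (10 df) or paired (5 df).
- REML fits of equation 3 itself, three time points, 1,000 runs each: 6.0% with no clinic effect, and 9.5%, 15.5% and 26.6% at ρ = .01, .02 and .05 (Monte Carlo error about 0.7 to 1.4 points).
- REML fits with a clinic intercept variance of .05 but no clinic variation in change: 6.6%, within simulation error of the 6.0%. Clinic differences in level do not inflate the α3 test, so adding only a clinic intercept would not repair it.

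**Power of a clinic-level test.** With N = 498, d = 0.25 and the SD of change taken as 1, SE = √(4D/498). For ρ = 0, .01 and .02 this is .0896, .1062 and .1206. Two-sided power on 10 df is .71, .57 and .47. On 5 df, with no gain from matching, it is .61, .48 and .39.

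**The case against.** The strongest defence has four parts.

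- **Equation 3 is only an example in a journal article.** The full plan may add terms, and the text does commit to handling clinic-level correlation. It is true that the final analysis is not known to ignore clinics. But the additions announced are covariates, not random effects, and the hypothesis test is defined by this equation's α3. A written model that contradicts its own rationale is more than an omitted detail.
- **The PCP-only term follows from a stated assumption.** The sample-size section takes clustering between physicians within a clinic as practically nil. If that also holds for change over time, the clinic part of the inflation disappears. This stands as a condition on the finding. It is still a planning assumption, and the Data Analysis Plan cites the same source when it asks for a clinic-level ICC to be modelled.
- **Read literally, Y_ijt is a PCP-level outcome.** PCP variation in change would then sit in the residual and the 8% case would vanish. Clinic inflation would remain but be smaller. With 7 PCPs of 6 patients, the clinic ICC of a PCP's mean change is ρ/(ρ + (1 − ρ)/6) and D = 1 + 6 × that ICC, which gives about 9%, 13% and 21% at ρ = .01, .02 and .05. The missing index is more likely shorthand, since the text speaks of patients' observations.
- **Some stronger inferences go too far.** A reader might infer that the degrees of freedom count observations, but the article names PROC MIXED without a df method. A reader might also blame the absent pair term. Leaving it out ignores the matched design but does not itself inflate the error; it usually makes the test conservative.

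**Conclusion.** The point holds as a defect in the written model: equation 3 conflicts with the plan's own reason for a multi-level analysis, and its group-by-time test has no error term for clinic or PCP variation in change. The missing clinic-by-time and PCP-by-time terms are the cause.

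The inflation is conditional. It is nil if clinics and PCPs do not differ in change, and a clinic ICC of change of only .01 roughly doubles the nominal 5%. The 26% figure needs an ICC of .05 at clinic level, which nothing in the article supports as a best guess. A reader might conclude that the trial will be analysed as if clinics had not been randomised, with certain inflation. The article does not support that: PCP clustering in level is modelled, the equation is labelled an example, and no clinic ICC of change is given. All figures assume equal clinics of about 41.5 patients.

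**What to change.** Rewrite equation 3 with an explicit patient index and a covariance over time within patient. Add random effects for PCP and clinic together with random clinic-by-time and PCP-by-time effects. Test α3 against between-clinic variation with small-sample or between-clinic degrees of freedom (about 10, or 5 if pair is included). Keep those degrees of freedom even if the clinic-by-time variance is estimated as zero. An analysis of clinic mean changes does the same job more simply. State whether pair is in the model, and commit to this before data are seen.

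The specification itself takes a few lines of PROC MIXED. The real cost is wider intervals and lower power, on the figures above already below the planned 0.8 for a two-sided test with no clinic variation at all. Including pair costs a further 5 df, which pays only if matching removes enough variation. The sample size should therefore be recalculated together with the revised model, for a stated side of the test and a stated range of clinic ICC of change.

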#### iCanFit 2.0 Intervention Protocol

As illustrated in Figure 3, the iCanFit 2.0 intervention protocol includes four steps. First, after the eligible participants complete the informed consent forms, they will complete an HBA on an iPad (see Multimedia Appendix 1 for sample screenshots), which takes about 15 minutes. Right after completion, patients will receive a printed copy of the HBA summary report with colorful charts of their current level of physical activity compared to the recommended physical activity levels (see sample summary reports in Multimedia Appendix 1). Meanwhile, the same report will be printed out in the office of the PCP with whom the patient has an appointment. Second, the patient brings the HBA report into his/her appointment with the PCP and the report serves as a natural conversation starter to facilitate patient-provider communication and joint goal setting. Third, right after the patient’s appointment with the PCP in the primary care clinic, a health coach will meet with the patient, further explain the HBA report, and ensure the patient has set a long-term physical activity goal, if the patient has not set one with the PCP. The health coach will give the patient a Fitbit Flex 2 (Fitbit Inc) (see Multimedia Appendix 2 and section below about the device) and demonstrate how to use the device. The health coach will also help the patient to create an account on the iCanFit online community. The health coach will advise on how to set short-term (eg, weekly) goals, track and sync data, share progress with family and friends via Facebook, and obtain personalized feedback on the iCanFit online community. The counseling session will last 30 minutes; a photo-illustrative brochure with instructions on how to use the Fitbit as well as account information and reminders will be given to the patient. Fourth, the health coach will constantly monitor patients’ use of the Fitbit and iCanFit online community. Patients will receive incentives (eg, online badges, virtual coins, and honor levels) for meeting physical activity goals and updating their progress. Any questions posted on the iCanFit online community will be answered by the health coach within 12 hours. If a patient is “idle” for 2 weeks, the health coach will call the patient to offer help and address the patient’s barriers. Patients will also receive a brochure of safety tips (see Multimedia Appendix 3), which details possible adverse events during exercise and how to take action depending on the situation. For adverse events that need immediate medical attention, patients are advised to go to the nearest emergency room. For nonurgent matters, they can contact the health coach, who can assist with scheduling a clinic appointment with the patient’s PCP.

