#### Comparator

The patients in the control group will receive usual care enhanced with a Fitbit Flex 2, as shown in Multimedia Appendix 2. The Fitbit Flex 2 was released in 2016, costs US $75, and weighs a quarter of an ounce. It is compatible with iPhones and Android phones, only needs to charge once a week, syncs automatically with mobile phones within 20 feet, and easily syncs to a computer with a USB port. It tracks steps taken, stairs climbed, calories burned, distance travelled, and sleep time. Figure 4 illustrates the process of the comparator protocol. After eligible patients provide informed consent, they will first complete an HBA on an iPad while waiting for their appointment. Unlike patients in the intervention group, patients in the control group will not receive any reports from their HBA; after their appointment with the PCP, they will receive a Fitbit Flex 2 and a brochure explaining how to use the Fitbit and the benefits of regular physical activity. Patients in the control group will not be given any information about the iCanFit online community; neither will they receive counseling or monitoring from health coaches. Similar to the intervention group, control group patients will receive the safety tips of exercise brochure.

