## Results

The proposed protocol received a high score in a National Institutes of Health review, but was not funded due to limited funding sources. We are seeking other funding sources to conduct the project.

**Table 1 table1:** Data collected and instruments used in the survey.

Domain	Scale or indicators	Data collection mode	Number of items
Demographics	Age, gender, race/ethnicity, marital status, education, income, insurance, chronic conditions, and perceived health	Survey with patients at baseline	11
Technology use	eHealth literacy scale (E-HEALS), alpha=.78 [37]	Survey with patients at baseline	11
Physical activity	International Physical Activity Questionnaire, alpha=.76 [38]	Surveys with patients at baseline and follow-up	4
Quality of life (primary outcome)	12-Item Short Form Survey, alpha=.81 [39]	Surveys with patients at baseline and follow-up	12
Patient-physician communication	Provider Patient Communication Scale, alpha=.80 [40]	Surveys with patients at baseline and follow-up	4
Support from health care team	Patient Assessment of Chronic Illness Care (PACIC), alpha=.79 [41]	Surveys with patients at baseline and follow-up	11
Support from broader community	Perceived social support for diet and exercise, alpha=.78 [42]	Surveys with patients at baseline and follow-up	9
Total minutes of exercise per week	Total minutes of moderate-to-vigorous physical activity a week	Fitbit	Varies
Patient-provider communication	Number of questions sent by patient	iCanFit community	Varies
Patient engagement	Frequency of log-ins, syncs, and communication with iCanFit community and health coach	iCanFit community and follow-up survey	Varies
Moderate-to-vigorous physical activity (primary outcome)	Total minutes of moderate-to-vigorous physical activity a week	Fitbit	1
Overall experience with the iCanFit program	Experience of the intervention and follow-up, intention of continuing use of Fitbit and iCanFit community, and suggestions for improving the program	Follow-up survey	Varies
Secondary clinic outcomes	Weight, chronic condition, and number of sickness clinic visits and adverse events	Medical records	4

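### For Fitbit MVPA, the stated test of α3 detects only divergence between arms after the device is issued, not the difference in level that is hypothesised and powered

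*Protocol article*

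**What the plan says.** Under Power and Sample Size Calculations, "The primary outcome of the study is the total minutes of MVPA per week", and "MVPA is measured as “very active” and “fairly active” on Fitbit". Table 1 gives Fitbit as the only collection mode for this outcome. Self-reported activity (IPAQ) is a separate survey item, collected at baseline and follow-up.

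The hypothesis in the Data Analysis Plan is that "patients in the intervention group will have more MVPA per week than the control group". The sample size is derived for a difference of d = 0.25 between two population means.

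The model (equation 3) has one coefficient each for group (α1), time (α2) and their product (α3). Of the test for an intervention effect, the plan says: "Referring to equation 3, this is equivalent to testing the hypothesis H_0_: α_3_ = 0". A positive, significant α3 is read as benefit.

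On timing, the iCanFit 2.0 Intervention Protocol first gives the patient the HBA report. Next, "the patient brings the HBA report into his/her appointment with the PCP and the report serves as a natural conversation starter", with joint goal setting. The device comes in the third step, after that appointment: "The health coach will give the patient a Fitbit Flex 2 (Fitbit Inc"). For controls, the Comparator section says that "after their appointment with the PCP, they will receive a Fitbit Flex 2 and a brochure explaining how to use the Fitbit". No earlier wear period is described for either arm.

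**The concern.** An interaction with time measures an intervention effect when the first time point precedes the intervention, because the arms then start equal in expectation and all of the effect appears as divergence. Fitbit MVPA has no such point. By the first worn week, intervention patients have had the report, the PCP discussion and the coaching session. An effect already present that week is part of the group difference at the start of the record. That difference is α1, which is not tested, and only what happens afterwards enters α3.

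The hypothesis and sample size therefore concern one quantity and the test another. A programme that raises MVPA at once and holds the gain would look like no effect. A programme whose early gain partly fades would give an α3 of the opposite sign, even with more MVPA in the intervention arm throughout.

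**Working it through.** **The plan's own figures.** For d = 0.25, alpha 0.05 and power 0.80, a one-sided two-sample t-test needs 199 per arm, or 398, which is the stated figure. A two-sided test needs 252 per arm, or 504, so 398 is reproduced only one-sided. Then 398 × 1.25 = 497.5, rounded to 498, and 498/0.8 = 622.5 (622 stated). All of this is for a comparison of means.

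**Power for the level contrast.** 498 analysed with D = 1.25 is an effective 498/1.25 ≈ 398, or 199 per arm. With SD 1, SE = √(2/199) = 0.100 and 0.25/0.100 = 2.49. Power is Φ(2.49 − 1.645) = 80% one-sided and Φ(2.49 − 1.96) = 70% two-sided.

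**Power for α3.** The protocol states neither the effect profile, the time points for Fitbit MVPA nor the within-patient correlation ρ. I assume:
- the first worn week is the first TIME point;
- the time points are first week, 3 months and 6 months, scaled 0, 0.5 and 1;
- compound symmetry holds, with ρ from 0.5 to 0.8.

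The squared deviations of TIME sum to 0.5, so SE(α3) = √[2(1 − ρ)/(199 × 0.5)] = √[4(1 − ρ)/199]. This is 0.100 at ρ = 0.5 and 0.063 at ρ = 0.8. α3 is expressed over the whole 6 months.

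| Effect profile (SD units) | α1 | α3 | α3 power, one-sided | α3 power, two-sided | 6-month level, one-sided / two-sided |
|---|---|---|---|---|---|
| 0.25 at once, sustained | 0.25 | 0 | 5% | 5% | 80% / 70% |
| 0.125 at once, rising to 0.25 | 0.125 | 0.125 | 35–63% | 24–50% | 80% / 70% |
| 0 at first, rising linearly to 0.25 | 0 | 0.25 | 80–99% | 70–98% | 80% / 70% |
| 0.25 at once, waning to 0.125 | 0.25 | −0.125 | below 1% | 24–50%, almost all in the negative direction | 35% / 24% |

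Example for row 2 at ρ = 0.5: 0.125/0.100 = 1.25; Φ(1.25 − 1.645) = 35% one-sided and Φ(1.25 − 1.96) = 24% two-sided. At ρ = 0.8: 0.125/0.063 = 1.97, giving 63% and 50%.

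**Sensitivity.**
- *Number of time points.* With 26 weekly values under compound symmetry, row 2 rises to 85% or more one-sided, because the slope is then estimated very precisely. Row 1 stays at 5%, and row 4 keeps α3 = −0.125.
- *Design effect.* Equation 3 has only a PCP random intercept, which cancels from a within-patient slope, so D = 1.25 is conservative for α3. Without it (249 per arm), row 2 gives about 29–60% two-sided with three time points.
- *What α3 estimates.* If the effect reaches 0.25 by one month and then stays level, α3 is 0.25 with three time points but 0.127 with 26 weekly ones. The 6-month difference is 0.25 in both cases.

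**The case against.** Five points can be made for the plan.

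- *The programme may work by build-up.* Patient Retention says participants will be advised to raise activity slowly, and the intervention relies on weekly goals, monitoring and online support. If the effect is zero in the first week and grows, α3 has 80–99% one-sided power and does at least as well as the 6-month contrast. This stands. A reader might infer that the α3 test cannot answer the hypothesis at all; the documents do not support that. They do not commit to a build-up profile either, and goal setting and coaching both take place on the first day.
- *A baseline exists.* A reader might infer that there is no pre-intervention activity measure. That is wrong: both arms complete the IPAQ within the HBA before the PCP visit. But it is self-report on another instrument. It can serve as a covariate, not as the first value of Fitbit MVPA.
- *Equation 3 is offered as an example, and this is a condensed article.* Time coding and Fitbit averaging windows may fairly be left to a fuller document. The test itself is stated, however, and it is the only one given for the main hypothesis. Added covariates do not change what α3 measures.
- *The form suits other outcomes.* This is correct. SF-12 and weight have true baselines, so the problem is confined to Fitbit MVPA.
- *A negative α3 is never said to mean harm.* This is also correct. The risk is that a real benefit is missed or appears with the wrong sign, not that the plan would declare harm.

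**Conclusion.** The point holds for the Fitbit MVPA primary outcome. The stated test addresses divergence after device issue, whereas the hypothesis and the sample size address level. This follows from the order of events in the text and needs no numerical assumption beyond taking the first worn week as the start of the record.

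The size of the consequence depends on the effect profile. The zero α3 for an immediate sustained effect and the negative α3 for a waning one hold at any correlation. The 35–63% one-sided range (24–50% two-sided) for the mixed profile rests on three time points, compound symmetry, ρ of 0.5 to 0.8 and D = 1.25, and it disappears with dense weekly data. A reader might set the lowest figure, 24%, against the planned 80%. That is not a fair comparison: 24% is two-sided at ρ = 0.5, while 80% is reproduced only one-sided. Like for like, the lowest values are 35% against 80% one-sided, or 24% against 70% two-sided.

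The case for change therefore rests mainly on what is estimated. The primary test should be corrected before the trial starts.

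**What to change.** For Fitbit MVPA, make the primary test the between-group difference in mean weekly MVPA at 6 months, from a model with time as a categorical factor, adjusted for the baseline IPAQ score. Do not treat first-week Fitbit data as a baseline, because in the intervention arm that week already follows the intervention. Keep α3 as a secondary description of trajectory. Equation 3 with the α3 test can stay for outcomes with a true baseline, such as SF-12 and weight.

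The cost is a reworded primary test, with no new patients and no new data, since the HBA already collects the IPAQ. There is one trade-off. If the effect does build from zero, the 6-month contrast has 80% one-sided power where α3 would have 80–99%. In return, the test matches the hypothesis and the sample size, and it keeps the right sign when an early gain partly fades.
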